# The Efficacy and Feasibility of an Interoceptive Exposure Technique for Preventing the Transition From Subacute to Chronic Back Pain by Altering the Emotional Response to Pain: Protocol for a Pilot Randomized Controlled Trial

**DOI:** 10.2196/45701

**Published:** 2023-10-19

**Keywords:** biomarkers, functional connectivity, interoceptive exposure, low back pain, prevention, subacute

## Abstract

**Background:**

Psychological factors such as stress, anxiety, mood, emotions, cognitive functioning, and pain behavior are relevant to the onset of pain and its continuation in the transition to chronic conditions. Subacute low back pain (LBP), a precursor to chronic LBP, is particularly poorly understood, and its relationships with psychological factors are understudied.

**Objective:**

We will conduct a study aiming to prevent the chronicity of subacute LBP by altering the emotional response to pain using an interoceptive exposure technique (IET). Considering the recent increase in knowledge about psychological risk factors, as well as recent findings in cognitive neuroscience regarding emotional and cognitive background factors in the LBP chronicity process, efforts should be made to discover effective preventive methods.

**Methods:**

We present a novel method aiming to prevent the transition from subacute to chronic back pain by altering the emotional response to pain using an IET. In this pilot randomized controlled trial, participants who are at a higher risk of LBP chronification due to the presence of a biomarker (ie, functional connectivity between the medial prefrontal cortex and nucleus accumbens) will be randomly assigned to the IET intervention group or control group A (treatment as usual). Participants who do not present with the biomarker will be assigned to control group B (treatment as usual) to assess how well this biomarker predicts the chronification of subacute LBP in this study population. Questionnaires measuring the pain experience and psychological distress will be used before the intervention, after the intervention (at 3 months), and at the 12-month follow-up.

**Results:**

This research project will combine 2 novel methods: a biomarker as the inclusion criterion and an IET as the intervention. The comparative study design enables evaluation of the efficacy of the IET, as well as replication of the biomarker’s validity as a possible clinical screening method.

**Conclusions:**

If found to be useful, the IET would offer a cost-effective and reasonable way to develop treatment for acute and subacute back pain conditions. Potential benefits include increased pain management and quality of life for the individual patient with the addition of a potentially useful functional pain management method at the societal level.

**Trial Registration:**

ClinicalTrials.gov NCT05450263; https://clinicaltrials.gov/ct2/show/NCT05450263

**International Registered Report Identifier (IRRID):**

PRR1-10.2196/45701

## Introduction

### Overview

As low back pain (LBP) has been shown to be highly prevalent and hence a major problem throughout the world, preventing LBP from becoming chronic can be considered a major challenge in pain medicine [1]. LBP prevalence rates between 3.9% and 20.3% have been reported [2], with the highest prevalence among female individuals and those aged between 40 and 80 years [3].

Although LBP episodes and associated disability usually improve within weeks, pain and disability typically continue, and recurrences are common [4]. The predictive power of biomarkers for chronic LBP has so far proven to be insufficient [5]. Risk factors for LBP may be genetic, acquired, or due to an individual’s interaction with the environment [6]. In a review of prospective studies, Linton [7] concluded that psychological variables such as stress, distress, anxiety, mood, emotions, cognitive functioning, and pain behavior were relevant to the onset of pain and its continuation in the transition to chronic conditions. The transition from acute localized LBP into chronic widespread LBP has shown relationships with the progression of both peripheral and central sensitization [8]. Furthermore, patients with chronic LBP might develop maladaptive behavioral strategies [9].

Recent brain imaging studies have further supported the role of emotional factors in the LBP chronification process, revealing mental factors influencing pain conditions [10]. Even in acute pain states, emotional factors seem to directly influence neural pain processing, as shown in the brain imaging study by Orenius et al [11], in which a valence-independent emotion interacted with the pain processing in the secondary somatosensory cortex. Functional and emotional nonadjustment factors have been identified in the acute LBP chronification process [12], with emotional nonadjustment relating to helplessness and hopelessness. Furthermore, chronification does not simply implicate the presence of enduring pain symptoms; it signifies a complex process associated with alterations in cortical structure and function. Vachon-Presseau et al [13] emphasized the importance of the emotional brain (ie, the cortico-limbic system) in the modulation of acute pain and in the prediction and amplification of chronic pain. A functional magnetic resonance imaging (fMRI) study showed that chronification of LBP shifts brain representation from nociceptive to emotional neural circuits [14]. These findings indicate the pivotal role that the neural structures involved in emotional learning play in the chronification of back pain [15]. Furthermore, the strength of synchronicity (ie, functional connectivity) between the medial prefrontal cortex (mPFC) and nucleus accumbens (NAc) was predictive (with >80% accuracy) of individuals who would subsequently transition from subacute pain to chronicity at a 1-year follow-up [15].

Neuroimaging studies have shown that cognitive behavioral therapy can change anxiety-related dysfunctions (phobia, traumatic stress, obsessive-compulsive disorder, and panic) of the nervous system [16]. Brain regions associated with attention, interoception, and sensory processing, including the prefrontal cortex and right anterior insula, are thicker in meditation participants than in matched controls, with the thickness of 2 regions correlating with meditation experience [17]. It has also been shown that mindfulness-based stress reduction techniques (a subcategory of cognitive behavioral therapy) produce macroscopic cortical plasticity in the adult human brain, demonstrating a dynamic relationship between behavioral state and cerebral anatomy [18]. Stress reduction correlated with structural changes in the amygdala after an 8-week mindfulness-based stress reduction intervention, demonstrating an association between neuroplastic changes and corresponding improvements in a psychological state variable [19]. An anatomical likelihood estimation meta-analysis showed that 8 brain regions were consistently altered in meditators, including areas key to meta-awareness, exteroceptive and interoceptive body awareness, memory consolidation and reconsolidation, self-regulation and emotion regulation, and intra- and interhemispheric communication [20]. Therefore, psychological interventions can produce both objective structural changes and alterations in the neural processing of emotions.

The treatment of chronic LBP has not primarily focused on removing an underlying organic disease but rather, within a biopsychosocial framework, on identifying the underlying mechanisms driving the disorder and thus enabling treatment to favorably influence the outcome [21]. Psychological methods targeting therapeutic processes relate to attention, cognition, emotions (including emotion regulation), and overt pain behaviors [22]. Despite a growing knowledge of relevant background factors in the transition from acute to chronic LBP [23], insight into preventive psychological methods applicable to subacute (4-12 weeks) LBP, a precursor to chronic LBP, is still particularly scarce. Insufficient theoretical guidance and integration in the design, selection, and delivery of methods that precisely target known dysfunctional behavioral processes have been presented as plausible shortcomings [24]. A recent systematic review showed that psychological interventions aiming to prevent chronification of subacute LBP had an insignificant preventive impact on pain measures [25].

### Aims and Objectives

There is a shortage of studies on interventions to prevent the chronicity of subacute back pain [25]. Considering the recent increase in knowledge about psychological risk factors, as well as recent findings in cognitive neuroscience regarding emotional and cognitive background factors in the LBP chronicity process, efforts should be made to discover effective preventive methods. Therefore, we will conduct a study aiming to prevent the chronicity of subacute LBP by altering the emotional response to pain using an interoceptive exposure technique (IET).

The aims of this study are as follows:

A pilot study will address the efficacy and feasibility of IET in preventing the chronicity of subacute pain. Participants who are found to have a higher risk of pain chronification due to the presence of a biomarker (functional mPFC-NAc synchronicity) will be randomized to the intervention group (n=7) or control group A (n=7; treatment as usual). To assess how well this biomarker predicts LBP chronification, participants who are not found to have the biomarker will be assigned to control group B (treatment as usual) without a defined number of participants.A full-scale study (intervention group: n=20; control group: n=20) will address the efficacy and feasibility of the IET in the prevention of subacute LBP chronicity with the same parameters as in the pilot study.

## Methods

### Participant Selection and Sampling Strategy

All participant recruitment will take place through the pain clinic at the Orton Orthopaedic Hospital and another private occupational health center. All study participants will be outpatients at the pain clinic and the private occupational health center. They are working-aged Finnish citizens who speak Finnish as their first or second language. A health care professional will diagnose the participants’ back pain and assess them based on the inclusion and exclusion criteria.

The inclusion criteria approximately correspond to those of Baliki et al [15]: pain intensity >40/100 on the numeric rating scale (NRS) [26] and back pain duration <16 weeks. Deviating from the abovementioned criteria, we limit the pain duration time more precisely (ie, to 4-10 weeks) to enable commencement of the IET before exceeding the valid 12-week time limit for pain chronicity. Additionally, it will be implied that participants experience at least occasional back pain when lying on their backs. Exclusion criteria resemble those of Baliki et al [15]: other chronic painful conditions, systemic disease, history of head injury, psychiatric diseases, or more than mild depression (score >19), as defined by Beck Depression Inventory-II (BDI-II) [27]. As an addition, exclusion criteria also include self-reported earlier diagnosed prolonged LBP episodes and longer sick leaves due to LBP.

A health care professional (physician or physiotherapist) will ask patients with subacute back pain if they are willing to participate in the study. When a patient is willing to participate, the research secretary will contact the patient and check that he or she meets the research criteria. Then, the health care professional will provide the patient with information about the study procedure and deliver the information and a consent form to the patient, who will sign the consent document. The patient will be told that he or she has the right to stop his or her participation at any time without having to explain the reason. The participant, accompanied by the research secretary, will undergo an fMRI scan and fill out the questionnaires. The feedback from the lumbar magnetic resonance imaging (MRI) will be given to the participants by the clinician. If necessary, proper further examinations and treatments will be provided, and the participants will be excluded from the study.

### Neuroimaging and Data Acquisition

All participants will undergo an fMRI measurement at the Advanced Magnetic Imaging Centre, Aalto University, Espoo, Finland, to determine if they meet the criteria for the biomarker (mPFC-NAc synchronicity), according to the study by Baliki et al [28]. The fMRI is done only in the initial stage, and no post-IET measurement is done to demonstrate possible effects on the biomarker.

The fMRI data will be collected with a 3T Magnetom Skyra whole-body scanner (Siemens Healthineers) and a standard 32-channel head coil. Anatomical T1 magnetization prepared–rapid gradient echo images will be acquired with the following parameters: orientation=sagittal; repetition time (TR)=2530 ms, time to echo (TE)=33 ms; 176 slices, slice thickness=1 mm, gap=50%; phase encoding direction=A-P; field of view=256 mm; and flip angle=7°.

Next, fMRI images will be acquired with a T2* weighted echo planar imaging sequence with the following parameters: orientation=transversal; TR=1570 ms, TE = 30 ms; 38 interleaved slices with no gap, slice thickness=3 mm; phase encoding direction=R-L; field of view=220 mm; flip angle=70°; base resolution=74; and 400 time points/volumes. A total of 4 dummy scans will be acquired for signal stabilization.

We will collect 1 anatomic MRI and 1 fMRI series for each participant. Throughout the fMRI acquisition, the participants will be asked to rate their LBP on a sliding cursor from “no pain” to “worst imaginable pain” (0-10). Participants will be given the following instructions (in Finnish): “Continuously rate the intensity of your low back pain. Indicate the intensity of your low back pain and changes in it by adjusting the cursor to the location corresponding to the intensity of your pain.” Participants will give their answer with a handheld 2-button device. Participants’ answers will not be recorded.

### Functional Connectivity Analysis and Participant Grouping

The functional mPFC-NAc connectivity of each participant will be analyzed with data processing assistant for resting-state fMRI [29]. Slice timing correction will be performed using the first acquired slice (slice number 2) as the reference slice. Images will be realigned, and normalization will be completed using a new segment and the diffeomorphic anatomical registration through exponentiated lie (DARTEL) algebra algorithm [30]. Images will be smoothed by DARTEL using a Gaussian kernel of full width at a half-maximum of 5 mm. Nuisance covariate regression will be performed with the Friston 24-parameter model. White matter signals and cerebrospinal fluid signals will be used as covariates. A 0.01 to 0.1 Hz filter will be applied. The functional region of interests, defined according to the criteria of Baliki et al [28], are spheres with a 10-mm radius. Talairach seed coordinates for the mPFC (x=2, y=52, z=–2) and right NAc (x=10, y=12, z=–8) will be transformed into Montreal Neurological Institute coordinates before calculating mPFC-NAc synchronicity. Participants with z(r) ≥0.25 will be classified as having an increased risk for LBP chronification.

Participants who are found to have a higher risk of pain chronification due to the presence of a biomarker (mPFC-NAc synchronicity) will be randomized to the intervention group (IET) or control group A (treatment as usual). To assess how well this biomarker predicts the chronification of LBP, participants who are not found to have the biomarker will be assigned to control group B (treatment as usual).

Participants who fit the inclusion criteria (based on fMRI) will undergo a lumbar spine MRI examination (1.5 Tesla) to rule out specific causes of the low back symptoms (ie, tumors, evidence of ankylosing spondylitis) or other conditions requiring special attention. Furthermore, the lumbar MRI ensures the homogeneity of the study population. The feedback from the MRI examination will be given to the participants by the clinician briefly in the style of “no specific causes or special factors to be taken into account,” after which the participants will participate according to the protocol. If necessary, proper further examinations and treatments will be provided, and the participants will be excluded from the study.

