### Data Collection and Statistical Analysis

Data will be obtained before the fMRI, 3 months after completing the IET, and 12 months after the fMRI. Data will be compared between the groups (IET vs treatment as usual in control groups A and B). The data will be analyzed using a repeated-measures analysis (mixed models).

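### The only stated use of the biomarker in assessing prediction is group membership at z(r) 0.25; a prespecified analysis of the z(r) value itself should be added beside it.

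*Protocol article*

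**What the plan says.** The Introduction (Overview) describes the predictor as a graded quantity: "the strength of synchronicity (ie, functional connectivity) between the medial prefrontal cortex (mPFC) and nucleus accumbens (NAc) was predictive", with accuracy above 80% for the transition to chronic pain at one year.

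Under Functional Connectivity Analysis and Participant Grouping, a value is obtained for everyone: "The functional mPFC-NAc connectivity of each participant will be analyzed with data processing assistant for resting-state fMRI". It is then cut once: "Participants with z(r) ≥0.25 will be classified as having an increased risk for LBP chronification". High-risk participants are randomized to IET or control group A. The means of assessing prediction is given as placing the biomarker-negative participants in group B: "To assess how well this biomarker predicts the chronification of LBP, participants who are not found to have the biomarker will be assigned to control". Aims and Objectives says the same, with 7 in the intervention group, 7 in group A and no defined number in group B.

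Data Collection and Statistical Analysis says: "Data will be compared between the groups (IET vs treatment as usual in control groups A and B"), using repeated-measures mixed models. No section uses the z(r) value after allocation. The Abstract and the Results section both name replication of the biomarker's validity, as a possible clinical screening method, as something the design makes possible.

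**The concern.** A threshold is needed to decide who is randomized. It is not needed to ask how strongly connectivity predicts later pain. If group label is the only form in which the biomarker enters, a participant just above 0.25 counts the same as one far above it, and one just below counts the same as one near zero.

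Two things are at stake for the replication aim. First, precision is lost in a pilot that has very little to spare. Second, the answer depends on one cut: a weak A-versus-B difference would not show whether connectivity fails to predict or whether 0.25 is a poor dividing line on this scanner and processing pipeline.

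**Working it through.** The protocol gives no power or precision figure for the biomarker aim, so there is none to reproduce. Three checks follow.

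**1. Information kept after splitting.** For a normal marker with a linear effect and a share p above the cut c, the relative efficiency of the split is φ(c)² / [p(1−p)]. The protocol does not give p, so it is varied.

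- p = 0.5: 0.637, equivalent to needing 1/0.637 = 1.57 times as many participants
- p = 0.3: 0.576, or 1.74 times
- p = 0.2: 0.490, or 2.04 times

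With 7 in A and an assumed 7 in B, the 50:50 figure means that 14 participants inform the question about as well as 0.637 × 14 ≈ 9 would with the value kept.

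**2. Power, split versus continuous.** This was simulated (4,000 runs, two-sided 0.05), comparing a t-test of A against B with a test of the correlation in the same treatment-as-usual participants. Half the population is assumed to lie above the cut. The correlation ρ between z(r) and 12-month pain and the size of B are also assumptions.

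| A, B | ρ = 0.3 | ρ = 0.5 | ρ = 0.7 |
|---|---|---|---|
| 7, 7 | 14% vs 19% | 33% vs 49% | 65% vs 87% |
| 7, 14 | 17% vs 26% | 42% vs 66% | 80% vs 96% |
| 20, 20 | 33% vs 47% | 76% vs 93% | 99% vs 100% |

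The first figure in each cell is the split and the second is the continuous analysis. The 20 in A is the control-group size given for the full-scale study in Aims and Objectives.

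**3. Precision of one z(r) value.** Neuroimaging and Data Acquisition gives 400 volumes at "TR=1570 ms, TE = 30 ms", and "We will collect 1 anatomic MRI and 1 fMRI series for each participant". The band-pass filter is 0.01 to 0.1 Hz.

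- Run length: 400 × 1.57 s = 628 s
- Effective observations, taken as 2 × bandwidth × duration: 2 × 0.09 × 628 = 113
- SE of z(r): 1/√(113 − 3) = 0.095
- Deducting 26 nuisance regressors (24 motion, white matter, cerebrospinal fluid): 1/√(113 − 26 − 3) = 0.109
- 95% interval around 0.25: about 0.06 to 0.44, or 0.04 to 0.46 with the deduction

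On these figures a participant whose true value is 0.05 from the cut is put on the wrong side 30–32% of the time. At a distance of 0.10 it is 15–18%, and at 0.20 it is 2–3%. This covers within-run error only.

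The same error reaches a continuous analysis. The slope is multiplied by SD²/(SD² + SE²), where SD is the true between-person spread, which the protocol does not give. With SE 0.10:

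- SD 0.15: 0.0225/0.0325 = 0.69
- SD 0.30: 0.09/0.10 = 0.90

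**The case against.** **A threshold suits a screening question.** The stated aim is validity as a screening method, and the cited result is an accuracy, which is a classification measure. Comparing people above and below a threshold fixed in advance answers that directly and avoids choosing a cut from the data. This stands, and it is why the contrast at 0.25 should be kept and not displaced by a slope.

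**The analysis plan is not shown.** A reader might infer that the biomarker will be tested only as A versus B and that the measured strength is thrown away. The document does not support that. The analysis section names no explicit A-versus-B test, excludes no regression on z(r), and does not say the values are dropped. A continuous analysis could sit in a document not at hand. What remains is narrower: the protocol does name a means of meeting this aim, and that means is group membership.

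**Single-scan noise is not cured by the change.** A reader might also infer that one run makes the grouping unreliable and that a continuous analysis would repair this. The protocol gives no reliability figure, and the SE of about 0.1 rests on an approximation. Overall misclassification ranges from about 9% to 27% as the assumed true SD falls from 0.30 to 0.10. The same noise flattens the slope, so a flat slope could still mean poor measurement. Only the loss from splitting and the dependence on one threshold are recovered.

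**The pilot is small either way.** This also stands. With 7 in each group and ρ up to 0.5, both analyses have power below 50%. The protocol concedes the small pilot sample as a weakness.

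**Conclusion.** The concern holds as a missed opportunity in the biomarker analysis. Group membership at 0.25 is the only stated use of the biomarker in assessing prediction, while a graded value is available for every participant and the rationale is about strength. The split keeps about half to two thirds of the information (49% at 20:80, 64% at 50:50). That result assumes a normal marker, a linear effect and the stated shares above the cut. The power gains further depend on an assumed correlation and an assumed size for group B.

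The point does not show that 0.25 is wrong or that it should not govern allocation. It does not touch the randomized IET-versus-A comparison.

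**What to change.** Leave allocation at z(r) ≥0.25 as it is, and keep the A-versus-B contrast at that cut as the screening-threshold result. Add one sentence to Data Collection and Statistical Analysis, for example:

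*For the biomarker objective, baseline z(r) will also be analyzed as a continuous predictor of NRS pain intensity 12 months after the fMRI in the treatment-as-usual participants (control groups A and B together), and the slope will be reported with its 95% confidence interval.*

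State as a limitation that z(r) comes from a single run, so measurement error will attenuate the slope.

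The cost is small. No further scan, participant or questionnaire is needed. The analysis assumes a linear form, which should be said. The article reports no enrolment as of September 2023, so at that date the analysis could still be prespecified.
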